#### Data Analysis

##### Overview

This is a 2-arm parallel RCT where the primary outcome is self-reported 30-day abstinence at 6 months. Questionnaires will be scored according to developer instructions. In the case of missing items, where developers do not have explicit instructions, we will use a half-mean imputation rule, as outlined in Bell et al [44]. All analyses will be adjusted for the randomization stratification. The primary analysis will use a significance level of .05; other tests will use a Bonferroni correction for multiple comparisons to control the overall type I error at 5%. Demographics, including sex, will be described with means, SDs, ranges, and frequencies or proportions and explored as correlates for successful tobacco outcomes using appropriate regression models.

##### Aim 1

We will test the efficacy of a telephone-delivered GI tobacco cessation treatment versus an evidence-based behavioral treatment on self-reported 30-day abstinence from smoking at T2. Secondary outcomes include self-reported and biochemically verified 7-day point prevalence abstinence at T2.

##### Hypothesis 1

Participants in the GIC will have 10% higher quit rates than those in the BC.

Generalized linear mixed models with a binomial distribution and a logit link will be used to model smoking outcomes. Time will be used categorically to avoid model misspecification, and the indicators for the stratified variables (ie, location and recruitment method) will be included in the models as covariates to control for the study design variables. Comparisons between the intervention and control groups at 3 and 6 months will be carried out using contrasts within these models. Mixed models are robust to missing outcome data (with respect to bias) and consistent with an intention-to-treat analysis; in addition, they yield more power than chi-square and *t* tests [42,43,45-47]. Secondary outcomes measured over time, including self-reported abstinence, nicotine dependence, self-efficacy, and cravings, will also be analyzed with mixed models (linear for continuous outcomes and generalized linear with a logistic link for binary). Biochemically verified abstinence at 6 months will be analyzed with a logit regression model. Unadjusted and adjusted models will be fitted, with adjusted models including key covariates such as expectancy. Sensitivity analyses with respect to missing data will be undertaken if missing data rates for the primary outcome are >10% at the 6-month follow-up. Multiple imputation by chained equations using data that are associated with missingness, the outcome, or both will be included in the imputation model [16]. We will compare T0 characteristics of participants who drop out with those of participants with complete data.

##### Aim 2

We will conduct dose-response analyses on the effect of GIC adherence (measured by self-reported minutes of intervention use per week, the number of times GI skills practiced per week, the number of sessions attended, and coach-rated participant engagement in sessions) on abstinence at 6 months. We will also examine effects of the GIC and the BC on tobacco use for those participants who do not report abstinence at 6 months.

##### Hypothesis 2A

GIC participants who are more adherent will have higher rates of abstinence at 6 months.

##### Hypothesis 2B

Participants not reporting abstinence will report statistically significant reductions in tobacco use.

We will investigate a dose-response effect of intervention engagement using logistic regression for cessation at 6 months and linear regression for dependence, self-efficacy, and so on, with adherence. Mediation models using a causal framework will also be used [17]. We will compare self-reported tobacco use levels in GI participants who have not quit at 6 months with the control group using regression models and also investigate their changes from T0 use. Consumer satisfaction will be described with summary statistics.

##### Aim 3

We will conduct subgroup analyses of moderators (eg, recruitment method, location, sex, race and ethnicity, and the level of dependence) on tobacco cessation outcomes at 6 months and assess participants using a mixed methods approach (eg, surveys and in-depth interviews) for exploring subgroup differences.

Logistic regression models will be used to investigate effect modification of the intervention effect on abstinence at 6 months by various moderators. These regression models will include interaction terms, and if statistically significant, a stratified (by moderator) analysis will be performed and reported.

Qualitative interviews will be recorded, transcribed, and consensus coded for themes by 2 coders to guarantee intercoder reliability [48,49]. The team will document variation in the subgroups’ reported program use during the RCT, including perceptions of the program’s effectiveness and ease of use.

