#### Hypothesis 2B

GIC and BC participants who do not report abstinence will report statistically significant reductions in tobacco use.

#### Aim 3

We will conduct subgroup analyses of moderators (eg, recruitment method, location, sex, race and ethnicity, and the level of tobacco dependence) on tobacco cessation outcomes at 6 months and explore subgroup differences in participants using a mixed methods approach (eg, surveys and in-depth interviews).

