#### Outcomes

Our primary outcome is self-reported 30-day abstinence as measured at the 6-month assessment. Secondary outcomes include self-reported 7-day abstinence as well as biochemically verified 7-day abstinence at the 6-month assessment and, for nonquitters, cigarettes smoked per day.

We will also examine the effect of adherence to the GI on cessation outcomes, conduct subgroup analyses of moderators (eg, recruitment method, location, sex, race and ethnicity, and level of dependence) on tobacco cessation outcomes at 6 months, and use a mixed methods approach (eg, surveys and in-depth interviews) to explore subgroup differences in GI adherence and cessation outcomes.

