#### Power and Sample Size

A sample size of 1200 participants would yield 90% power to detect a difference in smoking cessation rates between the arms of 10%, assuming a control arm cessation rate of 0.30, a 20% dropout, and a noncontinuity-corrected chi-square test at a 2-tailed significance level of 5%. We believe that 10% is a clinically significant difference with positive public health implications. Although the control arm had a higher cessation rate in our pilot study (50%) [19], we believe that this rate was unusually high. Furthermore, the rates were self-report, not biochemically verified, which are estimated to be 10% to 50% lower [39]. It was also high compared with quitline cessation rates, which are closer to 30% to 40% [15,40].

This sample size also yields 90% power to detect small-to-medium standardized effect sizes for continuous secondary outcomes of Cohen *d*=0.28, using a Bonferroni correction to account for multiplicity (20 tests), assuming a 2-sided 2-sample *t* test. Aim 3 will investigate effect modification, which requires approximately 4 times the sample size (or, equivalently, results in a larger detectable effect size) [41]. Assuming that a subgroup of interest makes up 50% of the sample, we have 90% power to detect a difference in cessation rates of 0.141 and 80% to 90% power to detect standardized effect sizes of 0.26 to 0.30, assuming no multiple testing correction. We recognize that the inputs to these calculations are estimates only.

Table 2 displays a sensitivity analysis, showing power for control arm cessation rates of 0.20 and 0.40, dropout rates of 20% to 40% (typical range for cessation trials), and differences of 0.10 to 0.15, showing ample power for different scenarios. These power calculations are conservative; simulation studies demonstrate that mixed effects models (the proposed analyses [Data Analysis subsection]) yield more power than chi-square and *t* tests [42,43].

**Table 2 table2:** Sensitivity analysis (N=1200).

Dropouts, n^a^	Cessation rate: 0.20			Cessation rate: 0.40	
	Detectable difference: 0.10	Detectable difference: 0.15	Detectable difference: 0.10		Detectable difference: 0.15
240	0.95	0.99	0.88		0.99
360	0.92	0.99	0.83		0.99
480	0.87	0.99	0.77		0.98

^a^Dropout rate: 20% (n=240); 30% (n=360); 40% (n=480).

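### The Hypothesis 2B analysis sets GI non-quitters against the control group as a whole; restricted to non-quitters in both arms, it still would not be a randomised comparison

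*Protocol article*

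**What the plan says.** The Outcomes section makes the smoking level of those who did not quit a secondary outcome: "for nonquitters, cigarettes smoked per day". The Objectives state Hypothesis 2B for both arms: "GIC and BC participants who do not report abstinence will report statistically significant reductions in tobacco use". Aim 2 in the Data Analysis section uses the language of effects: "We will also examine effects of the GIC and the BC on tobacco use for those participants who do not report abstinence at 6 months". The sentence that specifies the analysis, under Hypothesis 2B in Data Analysis, says something different: "We will compare self-reported tobacco use levels in GI participants who have not quit at 6 months with the control group using regression models". It goes on to say that changes from T0 will also be examined. In that sentence the restriction to non-quitters is attached to the GI arm only.

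The status used for the restriction is in substance the trial's main endpoint: "Our primary outcome is self-reported 30-day abstinence as measured at the 6-month assessment". Hypothesis 1 expects treatment to move it: "Participants in the GIC will have 10% higher quit rates than those in the BC".

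The article gives no analysis of cigarettes per day in all participants and does not label the non-quitter comparison descriptive.

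**The concern.** There are two separate problems.

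First, the sentence that defines the analysis disagrees with the four places that define its purpose (Aim 2 and Hypothesis 2B in the Objectives, Outcomes, and Aim 2 in Data Analysis). Followed as written, it compares the GI arm's failures with a control arm that still contains its successes. That gap appears even when the two treatments are identical.

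Second, if control non-quitters are meant, both groups are still chosen by a status that arises after randomisation and that treatment is intended to change. If GI helps some additional smokers to quit and these tend to be lighter smokers, the remaining GI smokers are a heavier group than the remaining control smokers. Randomisation no longer balances the two.

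At stake is the interpretation of a named secondary outcome. A difference produced by selection could be reported as an effect of GIC versus BC. The other methods in the article deal with other matters: the mixed models with missing outcomes, the inverse probability weighting in Limitations with attrition, and the mediation models with a different question.

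**Working it through.** **Inputs from the article.** N = 1200, 20% dropout, control cessation rate 0.30, difference 0.10, two-sided 5% (Power and Sample Size); Bonferroni correction for 20 tests (same section). Equal allocation is assumed because the ratio is not stated. The article gives no figures for cigarettes per day (CPD), so every CPD value below is an assumption.

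**Step 1: the plan's own figure.** 600 × (1 − 0.20) = 480 per arm. The uncorrected chi-square test of 0.30 against 0.40 has power 0.902, against 90% stated. This reproduces, so 0.30 and 0.40 are used as the planning quit rates.

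**Step 2: the literal contrast.** Let m be the mean CPD of continuing smokers, equal in both arms, and let qC and qG be the quit rates in control and GI.

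- GI non-quitters: m
- Whole control arm, quitters at 0: (1 − qC) × m
- Literal contrast: m − (1 − qC) × m = qC × m
- All-participant difference: (1 − qG) × m − (1 − qC) × m = (qC − qG) × m

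| Assumed m | Literal contrast, qC = 0.30 | All participants, 0.30 vs 0.40 |
|---|---|---|
| 10 | +3.0 | −1.0 |
| 15 | +4.5 | −1.5 |
| 20 | +6.0 | −2.0 |

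The literal contrast does not depend on qG, so it takes the same value when the arms are identical. In 2000 simulated trials with no treatment effect (480 per arm, quit rate 0.30 in both, baseline CPD gamma with mean 15 and SD 8, continuing smokers at 80% of baseline), every one was significant against GI at 0.05/20 = 0.0025.

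**Step 3: both readings when heavier smokers quit less often.** Same baseline distribution; quit rates 0.30 and 0.40; quit odds falling 33%, 45% or 55% per 10 cigarettes (logit slopes −0.04, −0.06, −0.08 per cigarette); every non-quitter in both arms smokes 30% less than at baseline. The true effect in continuing smokers is therefore zero. Differences are GI minus control, in CPD.

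| Fall in quit odds per 10 cigarettes | Literal | Literal, T0-adjusted | Non-quitters in both arms | Same, T0-adjusted | All participants |
|---|---|---|---|---|---|
| 33% | +3.48 | +2.86 | +0.18 | 0.00 | −0.99 |
| 45% | +3.63 | +2.70 | +0.27 | 0.00 | −0.95 |
| 55% | +3.75 | +2.55 | +0.34 | 0.00 | −0.93 |

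With no link between smoking level and quitting, the non-quitter contrast is 0.00. With quit rates of 0.30 in both arms, the literal contrast is still +3.29 to +3.41. T0 adjustment clears the non-quitter contrast here only because baseline smoking is the sole route of selection in this model. It does not clear the literal one.

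**Step 4: size against sampling error.** Non-quitters number 480 × 0.70 = 336 in control and 480 × 0.60 = 288 in GI. The standard error of their difference is about 0.47 CPD, so the bias is 0.18/0.47 = 0.4 to 0.34/0.47 = 0.7 standard errors.

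**Step 5: a true benefit in continuing smokers.** With continuing control smokers at 80% of baseline and a further 3% cut under GI, the benefit in those who would smoke under either arm is about −0.4 CPD. The unadjusted non-quitter contrast shows −0.13, 0.00 or +0.15 when the odds ratio for not quitting, per SD of baseline CPD, is 1.5, 2 or 3.

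**The case against.** The strongest reply is that the literal reading is not the intended one. The Objectives, the Outcomes section and Aim 2 all point to non-quitters in both arms, so the +3 to +6 may come from one loosely worded sentence. That is probably right about intent. It does not remove the need for a correction, because the loose sentence is the one that specifies the analysis.

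On the intended reading the bias is small: under one standard error in Step 4, and at the corrected 0.0025 level unlikely to yield a significant finding. The same sentence also plans to look at change from T0, and its regression models do not exclude T0 smoking as a covariate. Either would reduce selection that runs through baseline smoking. This stands, but neither deals with unmeasured factors such as motivation.

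A reader might infer that the non-quitter comparison gives the wrong sign, because it shows +0.2 to +0.3 where the all-participant difference is about −0.95. The documents do not support that. The two figures answer different questions. In Step 3 the true effect in continuing smokers is zero, and the −0.95 comes from the extra quitters.

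A reader might also infer that the within-arm half of Hypothesis 2B ("Participants not reporting abstinence will report statistically significant reductions in tobacco use") mainly reflects regression to the mean. Eligibility sets no minimum number of cigarettes per day, and the article gives no figures to show this. The absence of a comparator limits what a within-arm reduction can say about GI, but it is not an error.

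**Conclusion.** The concern holds in two parts of unequal weight.

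- **Wording of the comparison.** As written it is mechanically biased against GI by the control quit rate times mean CPD: +3 to +6 at a quit rate of 0.30 and assumed means of 10 to 20. T0 adjustment leaves about +2.5 to +2.9 in the Step 3 model. The existence of the bias needs only that control quitters are kept and GI quitters dropped; its size in cigarettes rests on the assumed means.
- **Conditioning on abstinence.** With non-quitters in both arms the comparison is still not randomised and should not be called an effect of GIC versus BC. The illustrated bias is about +0.2 to +0.3 CPD, and zero if quitting is unrelated to smoking level. T0 adjustment reduces it but cannot remove selection through unmeasured factors. A masked or reversed true benefit appears in Step 5 only at assumed odds ratios of 2 to 3 per SD, so a general claim of sign reversal is not warranted.

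This affects one secondary outcome. The primary comparison is untouched.

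**What to change.** 1. Make the between-arm analysis cigarettes per day at 6 months in all participants in the trial's analysis set, with abstainers at 0, adjusted for T0 cigarettes per day and the stratification factors (location and recruitment method). Use a two-part or rank-based model if the distribution is skewed.
2. Name the analysis set. All randomised participants should be used where T2 data exist, otherwise those enrolled. The RCT Protocol and Limitations sections count people as participants only after session 1 and report outcomes for enrolled participants, so T2 data on everyone randomised cannot be taken for granted.
3. Correct the Hypothesis 2B sentence so that the same non-quitter restriction applies in both arms, and say whether not having quit is judged on the 30-day or the 7-day definition.
4. Present non-quitter levels and changes from T0 by arm as descriptive, without a causal between-arm claim.

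The cost is analysis wording only. Table 1 already schedules tobacco use at T0 and T2, and primary results are not expected until 2027. The one drawback is that the all-participant estimate partly reflects the difference in quit rates and so overlaps with the primary outcome; the descriptive non-quitter results alongside it show how much smoking remains among those who did not quit.

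### Subgroup-specific effects are to be produced and reported only if the interaction test is significant, which leaves moderate moderation mostly without subgroup estimates and, on average, exaggerates what is reported

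*Protocol article*

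**What the plan says.** The Aim 3 paragraph of the Data Analysis section announces "subgroup analyses of moderators (eg, recruitment method, location, sex, race and ethnicity, and the level of dependence") on cessation at 6 months. The method is logistic regression with interaction terms, and "if statistically significant, a stratified (by moderator) analysis will be performed and reported". Fitting the interaction models carries no condition. Carrying out the stratified analysis, and reporting it, does.

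Two other places bear on how hard the gate is to pass. Data Analysis, Overview, reserves the unadjusted 5% level for the primary analysis and states that "other tests will use a Bonferroni correction for multiple comparisons". Power and Sample Size concedes that "Aim 3 will investigate effect modification, which requires approximately 4 times the sample size", and gives the Aim 3 detectable difference (0.141 at 90% power) without any adjustment for multiplicity.

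Aim 3 itself is announced unconditionally in Objectives, Outcomes and Data Analysis. The Limitations section keeps community recruitment in Arizona so that outcomes can be examined by state. None of these places promises subgroup-specific estimates when the interaction is not significant.

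**The concern.** The gate is a test that the article itself describes as short of sample size. A threshold on such a test does two things. It leaves moderators with real but moderate differences without subgroup-specific results, and readers tend to take that as evidence of no difference. It also selects, among the moderators that pass, those whose estimates happened to be large, so the published contrasts are too big on average.

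Aim 3 asks for whom guided imagery works better than standard behavioural treatment. State-specific effects, for which Arizona recruitment is being kept, would appear only if the location interaction were significant.

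**Working it through.** **Inputs.** From Power and Sample Size: 1200 participants, 20% dropout, control rate 0.30, target difference 0.10, two-sided 5%, and, for Aim 3, "Assuming that a subgroup of interest makes up 50% of the sample". Assumed here: 1:1 allocation (the ratio is not stated), equal dropout across cells, control rate 0.30 in both subgroups, average effect 0.10. Analysed: 1200 × 0.80 = 960, or 480 per arm, or 240 per arm in each half.

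**The plan's own figures.** Uncorrected two-proportion test, power = Φ[(d − 1.96·√(2p̄(1−p̄)/n)) / √(p₁(1−p₁)/n + p₂(1−p₂)/n)].
- Primary, 0.30 v 0.40, n = 480: (0.100 − 0.0603)/0.0306 = 1.295, power 0.902 (stated 90%).
- Aim 3, 0.30 v 0.441, n = 240: (0.141 − 0.0864)/0.0436 = 1.252, power 0.895 (stated 90%).

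So 0.141 is reproduced as a treatment effect inside one half of the sample. It does not describe the interaction test that forms the gate.

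**The gate.** With true effects 0.10 + δ/2 and 0.10 − δ/2 in the two halves, the interaction on the risk-difference scale is δ, with SE = √(Σ p(1−p)/240) over four cells. For δ = 0.10 the cells are 0.30, 0.45, 0.30 and 0.35:

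SE = √((0.21 + 0.2475 + 0.21 + 0.2275)/240) = √(0.895/240) = 0.061.

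Probability of passing ≈ Φ(δ/SE − z), with δ/SE = 1.64:
- alpha 0.05: Φ(1.64 − 1.96) = 0.37
- alpha 0.01 (0.05/5 named moderators): Φ(1.64 − 2.58) = 0.17

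Mean estimate given a pass ≈ δ + SE·φ(k)/(1 − Φ(k)), with k = z − δ/SE:
- alpha 0.05, k = 0.32: 0.10 + 0.061 × 1.01 = 0.16
- alpha 0.01, k = 0.94: 0.10 + 0.061 × 1.48 = 0.19

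Simulation with 2 million draws agrees (1.62 and 1.90 times the truth). The same steps over a range:

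| True difference | Pass, alpha 0.05 | Exaggeration | Pass, alpha 0.01 | Exaggeration |
|---|---|---|---|---|
| 0.05 | 13% | 3.0× | 4% | 3.6× |
| 0.10 | 37% | 1.6× | 17% | 1.9× |
| 0.141 | 64% | 1.25× | 40% | 1.4× |
| 0.20 | 91% | 1.05× | 77% | 1.1× |

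**Break-even.** A true difference passes half the time when it equals the smallest estimate that can pass: 1.96 × 0.061 = 0.12 at 0.05, and 2.58 × 0.061 = 0.16 at 0.01. A true 0.10 therefore cannot pass in the right direction without being overestimated.

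**Planned scale.** On the logit scale, power at 0.05 is 12%, 33%, 58% and 87% for the four rows. For a true 0.10 at alpha 0.01 it is 15%. Exaggeration for a true 0.10 is 1.7 and 2.0 times.

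**Uneven subgroups.** With a 20%/80% split, power at 0.05 falls to 25%, 45% and 74% for differences of 0.10, 0.141 and 0.20.

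**The case against.** The strongest reply is that testing the interaction before quoting stratum-specific effects is a standard guard against over-reading subgroups. The low power comes from the sample size, which the article acknowledges, and reporting more would not raise it. Aim 3 has no formal hypothesis and is exploratory. A forest plot of all subgroups could well be left to the analysis plan or the results paper. All of this is fair, and it limits the weight of the point. It does not remove it, because the article is not silent: it states a rule under which the p value decides whether subgroup results are produced and reported.

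Some stronger readings are tempting and go too far.
- A reader might infer that non-significant moderators leave no estimate at all. The interaction models are fitted for every moderator, and nothing says their coefficients will be withheld. What is missing is a commitment to subgroup-specific effects, and a logistic interaction coefficient alone does not give quit-rate differences by subgroup.
- A reader might infer that the gate hides most real moderation whatever its size. The article gives no expected size, and a difference of 0.20 would usually be found.
- A reader might infer that every reported difference will be inflated. Selection inflates the average, and only slightly when the true difference is large.
- A reader might apply a 20-test correction to the moderators. The article uses 20 tests only for continuous secondary outcomes.

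**Conclusion.** The point holds as a cheap improvement. Under the assumptions above, true subgroup differences below about 0.12 (alpha 0.05) or 0.16 (alpha 0.01) are more often left without subgroup estimates than reported, and those that are reported are exaggerated on average. At a true difference of 0.10, as large as the trial's whole target effect, the pass rates are 37% and 17% and the mean reported differences 0.16 and 0.19.

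Which alpha applies is itself open. The Overview places all non-primary tests under Bonferroni without defining the family, while the Aim 3 power statement assumes no correction; these two passages need reconciling. The size of the effect depends on the true moderation, which is unknown, and on equal subgroups. The primary analysis is unaffected.

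**What to change.** Replace the conditional sentence under Aim 3 with an unconditional one. For each named moderator (recruitment method, location, sex, race and ethnicity, dependence), report the quit-rate difference in each subgroup and the interaction estimate, all with 95% confidence intervals, whatever the p value. Keep the interaction test, but only to guide interpretation, and state the alpha used for it.

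The cost is one extra table or forest plot, with no new data. The intervals will be wide. In a 50% subgroup with 0.30 v 0.40, SE = √((0.21 + 0.24)/240) = 0.043, so the half-width is 1.96 × 0.043, about 0.085. For the difference between subgroups it is 1.96 × 0.061, about 0.12. The results must therefore be labelled exploratory. Without the significance filter, the selection effect on the reported estimates disappears.
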